## Abstract

**Background:**

Peripheral artery disease (PAD) is caused by atherosclerotic occlusions in the legs. It affects approximately 8-12 million people in the United States alone, one-third of whom suffer from intermittent claudication (IC), defined as ischemic leg pain that occurs with walking and improves with rest. Patients with IC suffer a markedly impaired quality of life and a high perception of disability. Improving pain-free walking time is a primary goal of rehabilitation in this population.

**Objective:**

The nitric oxide (NO)-PAD trial is designed to compare the effects that 12 weeks of supervised exercise training, in combination with a high inorganic nitrate-content (beetroot [BR] juice) beverage or placebo (PL) beverage, has on clinical outcomes of exercise and functional capacity in two groups of PAD+IC patients: exercise training plus beetroot (EX+BR) and exercise training plus placebo (EX+PL). The primary aims of this randomized controlled, double-blind pilot study are to determine group differences following 12 weeks of EX+BR versus EX+PL in the changes for (1) exercise capacity: pain-free walking time (claudication onset time, COT), peak walk time (PWT), and maximal exercise capacity (peak oxygen uptake, VO_2peak_) during a maximal-graded cardiopulmonary exercise test (max CPX) and (2) functional capacity: 6-minute walk (6MW) distance. The secondary aims will provide mechanistic insights into the exercise outcome measures and will include (1) gastrocnemius muscle oxygenation during exercise via near-infrared spectroscopy (NIRS); (2) gastrocnemius muscle angiogenesis: capillaries per unit area and per muscle fiber, and relative fraction of type I, IIa, IIb, and IId/x fibers; and (3) vascular health/function via brachial artery flow-mediated dilation, lower-limb blood flow via plethysmography, and pulse wave velocity and reflection.

**Methods:**

A total of 30 subjects between 40 and 80 years of age with PAD who are limited by IC will undergo exercise training 3 days per week for 12 weeks (ie, 36 sessions). They will be randomized to either the EX+BR or EX+PL group where participants will consume a beverage high in inorganic nitrate (4.2 mmol) or a low-nitrate placebo, respectively, 3 hours prior to each training session.

**Results:**

Data collection from this study has been completed and is in the process of analysis and write-up. While the study is too underpowered—EX+BR, n=11; EX+PL, n=13—to determine between-group differences in the primary outcomes of COT, PWT, and 6MW, preliminary observations are promising with Cohen *d* effect sizes of medium to large.

**Conclusions:**

Exercise training is currently the most effective therapy to increase functional capacity in PAD+IC. If the addition of inorganic nitrate to an exercise regimen elicits greater benefits, it may redefine the current standard of care for PAD+IC.

**Trial Registration:**

ClinicalTrials.gov NCT01684930; https://clinicaltrials.gov/ct2/show/NCT01684930 (Archived by WebCite at http://www.webcitation.org/6raXFyEcP)

## Introduction

Peripheral artery disease (PAD) is caused by stenosis of the arteries in the lower limbs, leading to a reduction in blood flow to the legs [1]. It affects approximately 8-12 million people within the United States alone, one-third of whom suffer from intermittent claudication (IC), defined as ischemic leg pain that occurs with walking and improves with rest [2]. Patients with IC suffer a markedly impaired quality of life and a high perception of disability [3]. Consequently, improving pain-free walking time is an important clinical goal for these patients [4].

Thus far, interventions aimed at improving clinical outcomes in patients with PAD have been either surgical, pharmacological, or exercise based, with supervised exercise training identified as the current best intervention for improving functional outcomes such as peak walking time and pain-free walking time [5-7]. Exercise training has proven efficacy in improving vascular health and function for atherosclerosis-associated comorbidities such as obesity, hypertension, dyslipidemia, and type 2 diabetes mellitus [8-14]. Patients with PAD have marked impairments in the oxygen delivery and uptake pathway due to deficiencies in both vascular function—increased arterial stiffness, endothelial dysfunction, and decreased peripheral blood flow—and skeletal muscle composition and architecture—capillary density rarefaction, mitochondrial dysfunction, and a loss of oxidative (ie, slow-twitch) fibers [15-18]. As they result in a more glycolytic phenotype leading to earlier onset of fatigue and exhaustion, the skeletal muscle abnormalities have a detrimental effect on the delivery, uptake, and utilization of oxygen. While supervised exercise training can improve both the skeletal abnormalities [19] and vascular function [20] in these patients, improving the patient’s ability to acutely tolerate an exercise bout could lead to even greater efficacy in the exercise training intervention by allowing them to exercise at a greater intensity at each session. Thus, to identify the next best treatment for patients with PAD, there is a continued need to advance our current understanding of both the disease and optimal interventional therapies.

Dysfunction of the vascular endothelium is a hallmark of cardiovascular diseases, including PAD [21]. A key facet of this dysfunction is abnormal vessel reactivity, which is mediated in part by a reduction in nitric oxide (NO) production [22]. NO is diatomic free radical that plays an important role in modulating vascular tone and regulating blood flow. In healthy individuals, NO is produced endogenously by endothelial nitric oxide synthase in response to elevated shear stress at the arterial wall. Patients with cardiovascular disease, in particular those with PAD, lack the ability to endogenously increase vascular NO bioavailability, leading to significant dysfunctions within the vasculature.

Plasma nitrite (NO_2_^-^), while once considered to be a biologically inert marker of NO, has recently been identified as an alternative NO source that can be reduced to NO under low oxygen conditions, such as hypoxia or ischemia [23]. One established noninvasive mechanism for increasing plasma NO_2_^-^ is via oral consumption of inorganic nitrate (NO_3_^-^). Inorganic NO_3_^-^ is found in relatively high concentrations in green leafy vegetables and beetroot. When swallowed, inorganic NO_3_^-^ is rapidly absorbed in the small intestine and while a majority is excreted by the kidneys, up to 25% is retained and becomes concentrated in the salivary glands. When the saliva is secreted, commensal oral bacteria on the dorsal surface of the tongue reduce the NO_3_^-^ to NO_2_^-^, which is then swallowed and absorbed back into the circulation. NO_2_^-^ concentration peaks approximately 2.5-4 hours after inorganic NO_3_^-^ consumption [24,25]. The circulating NO_2_^-^ is further reduced to NO in hypoxic conditions; the NO_3_^-^ -NO_2_^-^-NO reduction pathway increases peripheral blood flow during exercise and leads to improvements in exercise tolerance.

NO_3_^-^ supplementation has shown mixed effects on exercise performance [26-30]. In healthy and athletic populations, NO_3_^-^ supplementation has decreased the oxygen cost of exercise [28,31], increased time to exhaustion [28], and improved time trial performance [26]. However, studies utilizing similar participant demographics have reported no effect of NO_3_^-^ supplementation on power output [32], time trial time [33], or submaximal exercise efficiency [34]. One proposed explanation for these mixed findings is the discovery that an individual’s level of aerobic fitness could impact the effectiveness of nitrate supplementation, with one study demonstrating reductions in the oxygen cost of exercise and improvements in time trial performance only in participants with a low-moderate level of aerobic fitness [35]. While this research into responders and nonresponders to nitrate supplementation is still in the early stages, this particular finding perhaps lends more support for nitrate supplementation’s potential efficacy in clinical populations with low aerobic capacity. Indeed, in clinical populations, most of the results have been positive: improvements in submaximal endurance, muscle contractile function, and exercise capacity in heart failure [36-38], as well as submaximal exercise endurance in chronic obstructive pulmonary disease [39]. Only a few studies showed no effect [40]. In patients with PAD, following a single acute dose of a high-nitrate-containing beetroot (BR) juice (18 mmol), which led to a five-fold increase in plasma nitrite in comparison to placebo (PL) [27], we have previously shown an 18% and 17% increase in treadmill walking claudication onset time (COT) and peak walk time (PWT), respectively. While initial results show promise, most of the studies have utilized acute dosing strategies and have been limited in both sample size and demographic diversity.

While exercise training is the current best intervention for patients with PAD, by allowing the patients to acutely train at higher intensities—due to improvements in oxygen delivery/uptake—resulting in a greater cumulative effect than exercise alone, the acute benefits of nitrate supplementation on exercise tolerance suggest a potential opportunity to further enhance the effects of exercise training [6].

The hypothesis of this study is that subjects with peripheral artery disease with intermittent claudication (PAD+IC) who undertake regular consumption of a high-inorganic nitrate (4.2 mmol) supplement in conjunction with 12 weeks of supervised exercise training (exercise training plus beetroot juice [EX+BR]) will experience a greater clinical benefit in pain-free walking time (COT, 6-minute walk [6MW]) and PWT than those undertaking exercise and a placebo beverage (exercise training plus placebo juice [EX+PL]) alone. Specifically, the primary aim of this study is to determine group differences (EX+BR vs EX+PL) in the changes in the following:

Exercise capacity: pain-free walking time (COT), PWT, and maximal exercise capacity/peak oxygen uptake (VO_2peak_) during a maximal-graded cardiopulmonary exercise test (max CPX).Functional capacity: 6MW distance.

Secondary aims designed to provide mechanistic insight into the exercise outcomes include the following:

Gastrocnemius tissue oxygenation during max CPX testing via near-infrared spectroscopy (NIRS).Gastrocnemius muscle angiogenesis: capillaries per unit area and per muscle fiber, and relative fraction of type I, IIa, IIb, and IId/x fibers.Vascular health/function via brachial artery flow-mediated dilation, lower-limb blood flow via plethysmography, and pulse wave velocity (PWV) and reflection.

## Methods

### Study Design

The NO-PAD trial is a pilot, randomized, double-blind, per-protocol design with four different assessment time points (see Figure 1). This study is registered with ClinicalTrials.gov (NCT01785524).

The first round of assessment will act as a baseline with no exercise intervention or supplementation. Following this, all participants will be randomized to groups consuming either a 70 mL (4.2 mmol nitrate) beetroot juice (Beet It, James White Drinks Ltd, Ipswich, UK) or an identical nitrate-depleted placebo. Participants will then repeat the baseline assessments, except for the muscle biopsy, but will consume their assigned beverage 3 hours prior to each visit.

Participants will continue consuming their beverage 3 hours prior to each of their 36 exercise training sessions. Periodically, subjects will be selected for unannounced blood draws at training visits to check plasma nitrate and nitrite concentrations. Post-exercise training, participants will complete the same assessments as the baseline visit while still acutely consuming their beverage before visits. Both groups will then stop consuming the beverage for at least 1 week prior to the final visit. The half-life of nitrate is 5-8 hours and as the supplementation protocol is three acute doses per week, a 1-week washout period should be sufficient to minimize any possible residual effect of the nitrate [41]. To maximize internal validity, study personnel, time of day, equipment, and order of testing will be consistent for each of the assessment time points.

**Figure 1 figure1:**
[figure not shown]
Study design with visit timeline and corresponding assessments. 6MW: 6-minute walk; BR: beetroot juice; COT: claudication onset time; max CPX: maximal-graded cardiopulmonary exercise test; NIRS: near-infrared spectroscopy; PL: placebo juice; PWT: peak walk time; VO2peak: peak oxygen uptake.

### Recruitment Strategies and Eligibility

We aim to recruit a total of 30 participants—equal numbers of men and women—between the ages of 40 and 80 years with diagnosed PAD from the clinics and community at Duke University Medical Center. We anticipate a dropout rate of approximately 15%-20% and, therefore, 24 patients out of the 30 (EX+BR, n=12; EX+PL, n=12) are expected to complete the study. This study will have continuous rolling enrollment until the recruitment goals are met. Subjects will be recruited primarily through collaboration with Duke University Medical Center cardiovascular physicians and vascular surgeons. Clinic medical records will be reviewed to prescreen patients for inclusion and exclusion criteria (see Textbox 1).

Inclusion and exclusion criteria for study screening visit.**Inclusion criteria:**1. Aged between 40 and 80 years.2. Diagnosed peripheral artery disease (ankle-brachial index <0.90) with intermittent claudication.3. No major changes in medications for at least 3 months.**Exclusion criteria:**1. Foot ulcers, advanced neuropathy, gangrene, or other musculoskeletal condition that could limit exercise performance.2. Type 1 diabetes or glycated hemoglobin >8.5%.3. A major cardiovascular event within the previous 6 weeks or a planned hospitalization within the next 2 months.4. Any cardiovascular condition that impacts safety of completing a cardiopulmonary exercise test, including history of significant left main or three-vessel coronary artery disease (>70% stenosis), recent myocardial infarction (6 weeks), chest pain during cardiopulmonary exercise test, or >2 mm ST depression during exercise; foot ulcers/advanced neuropathy or other musculoskeletal condition that could limit exercise performance.5. Allergy to beets or proton pump inhibitors.6. Refusal or inability to abstain from the use of proton pump inhibitors for 24 hours prior to testing.

Records of those criteria will be noted and the appropriate medical doctor will introduce the study to the patient. Patients who consent to being contacted by the research team will undergo a telephone screening questionnaire to determine if the study eligibility criteria are met. Eligible and interested patients will then attend an orientation visit and a consent meeting. During this initial visit, the study details will be explained verbally and the individuals will have the opportunity to read over the approved informed consent document and ask any questions they may have about the trial. The patients can then choose to sign the informed consent form or decline participation. Following the consent visit, enrolled subjects will return on a separate day to undergo a physical examination and a review of their medical history and medications by the study physician. Participants will then be scheduled for their baseline assessment visits. Details of the testing occurring at each time point is outlined in Figure 1 and is described in detail in the Testing Methodology section.

### Supplementation

Following initial screening and baseline testing, subjects will be randomized to consume either a high-nitrate-containing beetroot beverage or a low-nitrate placebo throughout the duration of the exercise training. Randomization should ensure the groups are initially equal within either the EX+BR or EX+PL intervention. Both groups will be instructed to consume one 70 mL bottle of beetroot juice (containing 4.2 mmol inorganic nitrate) 2.5-3 hours prior to every testing visit and training session between time point 2 and time point 3. The beetroot juice bottles will be identical in appearance and taste. The bottles will be color coded by a third party to ensure that the research staff remain blinded while providing the correct supplement to each participant.

Scheduled but unannounced blood draws will be performed throughout the study to confirm participants are conforming to their appropriate beverage allocations.

### Exercise Intervention

#### Overall Program and Attendance Requirements

All subjects will attend supervised exercise training sessions three times per week for a total of 12 weeks at the Duke Health and Fitness Center at the Duke University Medical Center for Living. Each session is structured to last approximately 45-60 minutes, including taking vital signs—heart rate and blood pressure (BP)—before and after the training session. To meet minimum exercise session attendance requirements, participants will need to complete 34 of the 36 exercise training sessions and should not miss more than 1 week of training (ie, 3 sessions) consecutively. Additional sessions will be added if necessary to ensure that an adequate exercise stimulus is given to each subject so that any decreases in fitness or function during unintended breaks are mitigated. The study will be analyzed under per-protocol criteria. Subjects who withdraw from the study prior to completion will be excluded from the final analysis. However, attrition rates will be reported and documented.

Participants will not be excluded due to current exercise habits, but all participants will be instructed to maintain their normal activity levels throughout the exercise intervention.

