### Statistical Analysis Plan

This is a repeated-measures design, with the purpose of assessing change over time for the two intervention groups. Since this is a pilot study, the overarching goal of the analyses is to derive effect sizes (ie, effectiveness) for this intervention for a future larger, confirmatory study. We will conduct the analyses chronologically in three phases: (1) descriptive analyses of dependent and independent variables; (2) bivariate analyses of the association between group membership and the outcome measures; and (3) controlled multivariable analyses, which assess the association between groups and the outcomes controlling for important covariates. Randomization should ensure the groups are initially equal; however, we will control for important baseline variables, including the two outcomes of interest. We will not control for any variables observed postrandomization [46]. Our general analytic strategy will be to employ these models to assess differences between groups and, most importantly, assess the differences in change over time between the groups. Our general baseline model will have the following form:

Y
_it_ = β
_0_ + β
_1_ (Group) + β
_2_ (Time
_t_) + β
_3_ (Group × Time
_t_) + β
_4_ (Covariates
_it_) + ε
_it_ (5)

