As noted previously, the results from this pilot study will be used to power a subsequent, larger, adequately powered confirmatory clinical trial of the impact of beetroot juice on the outcomes listed above. The results, along with theory and clinical significance, will guide the choice of the primary outcome(s) for that trial, with appropriate control for type I error. While the results of this pilot study will prove useful in the calculation of power, we are aware of the many risks of “playing the winner” in choosing to power a subsequent trial from pilot study results only [50,51].

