### Study Limitations

The small sample size and the focus on patients with PAD+IC only limit the ability to broadly apply the results of the study to the larger PAD population and to generalize these results to subsequent studies. This study also uses a per-protocol design with the intent that data may provide the physiological proof of concept for the intervention and allow us to derive variance data and effect sizes within and between groups to inform future studies, which will utilize an intent-to-treat criterion in the analytic structure.

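### The only planned analysis drops withdrawn subjects, yet its effect sizes are to power an intention-to-treat trial, which risks being under-sized if no discount is applied

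*Protocol article*

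**What the plan says.** The section on overall program and attendance requirements fixes the analysis population: "The study will be analyzed under per-protocol criteria", and "Subjects who withdraw from the study prior to completion will be excluded from the final analysis". It adds "However, attrition rates will be reported and documented", without saying whether by arm or with reasons. The same section sets an attendance requirement: "participants will need to complete 34 of the 36 exercise training sessions". Study Design also calls the trial a per-protocol design.

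Under Recruitment Strategies and Eligibility the target is "We aim to recruit a total of 30 participants". A dropout rate of 15% to 20% is anticipated, leaving 24 completers, 12 per group. The model in the Statistical Analysis Plan section is indexed over 24 individuals, which is the number of completers.

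That section states the purpose of the analyses: to "derive effect sizes (ie, effectiveness) for this intervention for a future larger, confirmatory study". It later says that "the results from this pilot study will be used to power a subsequent, larger, adequately powered confirmatory clinical trial". Study Limitations presents the per-protocol design as a proof-of-concept choice meant "to inform future studies, which will utilize an intent-to-treat criterion in the analytic structure". The article gives no analysis of all randomized subjects and no rule for discounting the per-protocol effect before it is used to size the next trial.

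**The concern.** Two problems follow from the same choice.

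The first is selection. Randomization protects the comparison of everyone randomized. Completion is observed afterwards and may depend on the beverage. The trial's own rationale is that nitrate improves exercise tolerance, and each session asks for 30 minutes of walking in claudication pain. If the rationale is right, the beverage could influence who finishes. The Statistical Analysis Plan section declines to adjust for variables seen after randomization, but restricting the analysis to completers conditions on exactly such a variable.

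The second is a mismatch of target. The pilot's main product is an effect size in completers. The trial that it feeds will count everyone randomized, including those who stop. If those who stop gain less, the intention-to-treat effect is smaller than the per-protocol effect, and a sample size based on the latter is too small.

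Some data that could help would also be set aside. By the visit order in Study Design, a subject who leaves during training has already been assessed at baseline and again on the assigned beverage.

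**Working it through.** **Inputs from the article.** Recruitment target 30; dropout 15% to 20%; power 80%; two-sided alpha 0.05; equal groups. The dropout allowance reproduces: 24 / (1 − 0.20) = 30.

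**Inputs assumed.** The article calls the observed effects medium to large but gives no numbers, so I take per-protocol standardized effects of d = 0.5 and d = 0.8. It gives no effect in withdrawn subjects, so I let k be the share of the added benefit that they keep, with k = 1, 0.5 and 0. The standard deviation is held constant, and the future trial is assumed to have the same withdrawal share f as anticipated here.

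**Formulas.**
- Intention-to-treat effect = d × [(1 − f) + f × k].
- Required sample size scales as 1 / [(1 − f) + f × k]².
- Sample size per arm and power come from the two-sample t-test.

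**Inflation factors.**
- k = 1: 1.00 at either withdrawal rate.
- k = 0.5: 1 / 0.925² = 1.17 at 15%; 1 / 0.90² = 1.23 at 20%.
- k = 0: 1 / 0.85² = 1.38 at 15%; 1 / 0.80² = 1.56 at 20%.

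**For d = 0.5, where the undiscounted calculation gives 64 per arm:**

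| Withdrawal | Share kept | Intention-to-treat effect | Needed per arm | Power at 64 per arm |
|---|---|---|---|---|
| 15% or 20% | all | 0.50 | 64 | 80% |
| 15% | half | 0.4625 | 75 | 74% |
| 20% | half | 0.45 | 79 | 71% |
| 15% | none | 0.425 | 88 | 66% |
| 20% | none | 0.40 | 100 | 61% |

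**For d = 0.8, where the undiscounted calculation gives 26 per arm:** with 20% withdrawal and no benefit kept, the effect is 0.64, 40 per arm are needed, and power at 26 is 62%.

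**Does ordinary dropout inflation cover this?** For d = 0.5 and 20%, 64 / 0.80 = 80 per arm. If all 80 are analysed, that is enough when half the benefit is kept (79 needed). It is not enough when none is kept: at an effect of 0.40, power is 71% and 100 are needed.

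**The case against.** The strongest reply is that the choice is open and reasoned. Study Limitations names the per-protocol design as a limitation, gives proof of concept as its purpose, and itself says that later studies will use intention to treat. The Statistical Analysis Plan section also warns against powering a trial from pilot results alone. Efficacy under adherence is a legitimate pilot target. This justifies keeping the per-protocol analysis, but not having it as the only one, and neither statement supplies a route from the completer effect to the intention-to-treat effect.

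A second reply is that sampling error is larger than this bias. With 11 and 13 completers, the standard error of d = 0.5 is about √(24/143 + 0.25/48) = 0.42, so a 95% interval runs from about −0.3 to 1.3, against a shift of at most 0.10. This stands as a matter of proportion. But a systematic shift is not removed by acknowledging imprecision, and this one can be examined at little cost.

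A third reply is that a likelihood-based model fitted to visits before withdrawal assumes that data are missing at random. It in effect predicts a withdrawn subject's final outcome from similar subjects in the same arm who stayed, so it would not by itself produce the diluted effects in the table. This is correct, and it is why the fix includes sensitivity analyses and a range of discounts.

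Three stronger readings are not supported:
- A reader might infer that everyone below 34 sessions is excluded. The article states exclusion only for withdrawals, and it allows sessions to be added.
- A reader might take 6 of 30 as the number lost after randomization. Consent and baseline testing come before randomization under Methods, so some losses could be earlier, although the abstract speaks of 30 being randomized.
- A reader might assume that most withdrawn subjects have the second assessment. The visit order makes it available for those who leave during training, but the article does not say how many that is.

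**Conclusion.** The mismatch is real: a completers-only effect size is destined for an intention-to-treat trial, with no all-randomized estimate and no discount stated. The comparison is also open to selection bias of unknown sign, because withdrawals by arm are not given.

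A reader might infer that the next trial will be under-sized. The documents do not support that. Its sample size has not been calculated in this article. A shortfall arises only if the effect is carried over undiscounted and withdrawn subjects lose some benefit, and unequal withdrawal could bias the completer contrast in either direction. What can be said is that there is a risk. It ranges from no shortfall (factor 1.00) to a required sample size about 1.56 times as large, under the assumed withdrawal of 15% to 20%, an unchanged standard deviation and the stated range for the benefit kept. This is worth correcting because the correction is cheap, and disclosure of the limitation does not make it unnecessary.

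**What to change.** 1. Add an analysis of all randomized subjects by assigned group, using a likelihood-based repeated-measures model with every available visit, including those of withdrawn subjects. State its missing-at-random assumption.
2. Add sensitivity analyses in which withdrawn subjects gain none, or half, of the added benefit.
3. Keep the per-protocol analysis as the proof-of-concept result.
4. Report withdrawals and any other exclusions by arm, with reasons.
5. State that the future intention-to-treat trial will be sized from the all-randomized estimate with an explicit range of discounts, not from the undiscounted per-protocol effect size.

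The cost is some further analysis of data already collected and, probably, a less favourable effect size. Data collection is complete and the article describes no follow-up after withdrawal. If none was done, the effect in withdrawn subjects cannot be estimated directly, and the discount remains an assumption to be shown as a range.
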